### Statistical Analysis

Publication of a full statistical analysis plan separate to this manuscript is planned. This will include details on planned interim and subgroup analyses. Outcome analyses will be undertaken on an intention-to-treat basis by the study statistician blinded to group allocation. The overall difference in proportion of participants dying in a preferred location between the intervention and control groups will be assessed using logistic regression. Secondary outcome analyses of quality of life and strain measures, collected multiple times from the same patient-carer dyad, will be performed by constructing random effects models with the intervention group variable interacted with time to account for within-dyad correlation. Health system outcomes will be assessed by including the intervention group variable in an appropriate count-based regression model that accounts for the variable exposure (length of time before death). Inclusion of baseline data in regression models will be used to explore additional variation within dyad characteristics.

Elements introduced to mitigate bias in the study include use of a computer randomisation service, blinded outcome assessment and intention to treat analysis.

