### Sample size

The study is powered to detect a significant difference in the primary outcome of death within the follow up period in the carer supported preferred location. Where the person with dementia has previously indicated a preferred location, this will be ascertained from and confirmed with the carer. Otherwise, the carer will be requested to nominate. Whilst there are large datasets that describe the location of death of people with advanced dementia, only two small studies from a recent systematic review provided data on preferred location of death [11].

Using this review to assume 60% of people with dementia in the control arm of the trial will die in a carer preferred location, then 408 participants will need to be enrolled in the study to have 90% power to detect a 15% increase in the proportion of people dying in preferred locations to 75%. The Type I error probability associated with these tests of this null hypothesis is 0.05. Applying a small (< 10% tolerance) to incomplete data and loss to follow up, we will enrol 440 participants, 220 per study arm.

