### Outcome measures

The primary outcome measure is the proportion of participants dying in their carer-nominated preferred location for death within 12 months of enrolment. The person-centred secondary outcome measures are changes in carer (proxy) reported and self-ratings of quality of life, symptoms and strain, using the same measurements done at baseline. Other secondary outcome measures will be health system focussed, namely.Number of ED attendances post enrolment (with and without subsequent admission to hospital)Hospital occupied bed days post enrolment, including hospital in the home admissionsDays spent in nominated preferred location of care post enrolmentNumber and type of medical interventions in last seven days of life e.g. IV fluids or antibiotics

Finally, if the person with dementia dies in the follow up period, we will measure bereavement risk in the carer using the Modified Bereavement Risk Index (MBRI) [20].

A recruiter blinded to the allocation arm of the carer will undertake all outcome measure assessments every three months post enrolment, for a maximum of twelve months. Participants will have the choice to enter questionnaire responses directly into an electronic database, or answer questions by phone with the recruiter recording their responses for them.

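### The stated main model for the repeated quality-of-life, symptom and strain scales does not include the same-scale baseline score, and baseline data get only an exploratory role; making it part of the main model would add precision at no cost

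*Protocol article*

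**What the plan says.** According to the Baseline assessment and Randomisation and control arm sections, QUALID, SAS, EQ5D and MCSI are all collected before allocation. The Outcome measures section defines the person-centred secondary outcomes as "changes in carer (proxy) reported and self-ratings of quality of life, symptoms and strain, using the same measurements done at baseline". It adds that a blinded recruiter "will undertake all outcome measure assessments every three months post enrolment, for a maximum of twelve months", which gives visits at 3, 6, 9 and 12 months.

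The Statistical Analysis section says that the analyses of quality of life and strain "will be performed by constructing random effects models with the intervention group variable interacted with time to account for within-dyad correlation". Symptoms are not named in that sentence. No other model is given for them, so I take SAS to be handled in the same way.

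The section's only statement on baseline data is: "Inclusion of baseline data in regression models will be used to explore additional variation within dyad characteristics". It opens with: "Publication of a full statistical analysis plan separate to this manuscript is planned".

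**The concern.** A group-by-time random-effects model can treat the baseline score in three ways.

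1. Baseline is the time-zero response and each arm has its own baseline mean. The group-by-time contrast is then a difference in change from baseline. It spends a parameter on a baseline difference that randomisation makes zero in expectation, and any chance imbalance enters the change score through regression to the mean.
2. Only follow-up scores are modelled. The baseline score is then unused.
3. The baseline score is a covariate in the main model, or the two arms share one baseline mean. This is the efficient form.

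The article does not say which is meant. The usual meaning of a group variable interacted with time, combined with outcomes defined as changes, points to the first. The exploratory wording on baseline data fits the third poorly. Under the first or second, the main estimate has wider confidence intervals than the same data allow.

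These scales carry the trial's evidence on quality of life and carer strain. The Sample size section sets numbers for the primary outcome only, so no precision has been secured for them. Leaving adjustment exploratory also invites an adjusted result that competes with an unadjusted main one.

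**Working it through.** **The plan's own figure.** The only sample-size figure is for the primary outcome. It assumes 60% against 75%, and the plan says "408 participants will need to be enrolled in the study to have 90% power to detect a 15% increase". With pooled variance and two-sided 0.05, the mean proportion is 0.675 and

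n per arm = [1.960·√(2·0.675·0.325) + 1.282·√(0.24 + 0.1875)]² / 0.15² = (1.298 + 0.838)² / 0.0225 ≈ 203.

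That is 406 in total, within 2 of the stated 408. The figure is reproduced and does not depend on the present point. The article states no SD, correlation or power for QUALID, SAS, EQ5D or MCSI.

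**Assumptions.** Equal correlation ρ between any two visits, taken as 0.3, 0.5 and 0.7; equal variance σ² at all visits; visits at 0, 3, 6, 9 and 12 months; 220 per arm.

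**Complete data, 12-month contrast.**
- Baseline means free: variance per dyad is 2σ²(1−ρ).
- Baseline-adjusted: σ²(1−ρ²).
- Ratio R = (1−ρ²) / [2(1−ρ)] = (1+ρ)/2 = 0.65, 0.75, 0.85.
- SE ratio √R = 0.81, 0.87, 0.92, so the unadjusted SE is about 24%, 15% and 8% larger.

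An effect with 80% power before adjustment has standardised size 1.960 + 0.842 = 2.802. Power after adjustment is Φ(2.802/√R − 1.960):
- ρ = 0.3: Φ(3.475 − 1.960) = 0.935
- ρ = 0.5: Φ(3.235 − 1.960) = 0.899
- ρ = 0.7: Φ(3.039 − 1.960) = 0.860

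If the comparator is follow-up scores only, R = 1−ρ² = 0.91, 0.75, 0.51. At ρ = 0.5 the power gain is the same, 80% to 90%.

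**Allowing for deaths.** Complete 12-month data are unrealistic in this population. I compared generalised least squares variances with free and with common baseline means, with linear loss from baseline to month 12, in two scenarios:
- 60% still observed in both arms at month 12. This is purely an assumption.
- 40% of control and 25% of intervention still observed. This reads the 60% and 75% of the Sample size section as proportions of everyone enrolled, so that at most 1 − 0.60 and 1 − 0.75 are alive.

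| Observed at month 12 | ρ = 0.3 | ρ = 0.5 | ρ = 0.7 |
|---|---|---|---|
| 100% in both arms | R 0.65, power 93% | R 0.75, power 90% | R 0.85, power 86% |
| 60% in both arms | R 0.75, power 90% | R 0.825, power 87% | R 0.90, power 84% |
| 40% control, 25% intervention | R 0.85, power 86% | R 0.90, power 84% | R 0.94, power 82% |

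Each row starts from 80% power with free baseline means in that same row. The gain shrinks with attrition because the free baseline means are still estimated from everyone enrolled, so their error is a smaller share of the total.

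**The case against.** The strongest reply is that the article never says the baseline score is left out. It names a class of model, and both efficient forms belong to that class. The same paragraph provides for baseline data in regression models. Defining an outcome as a change does not commit the trial to an unadjusted estimator, because a baseline-adjusted model also estimates the effect on change. Covariate lists and the parameterisation of baseline are details that a condensed article usually leaves to the analysis plan, and one is announced.

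Much of this stands. A reader might infer that the trial has ruled out baseline adjustment and will report a raw difference in change. The documents do not support that: no sentence excludes the baseline score, and the unseen plan may include it. What remains is that the article is not silent on baseline data. It gives them a purpose, and that purpose is exploratory and directed at dyad characteristics, which does not naturally describe the time-zero value of the outcome scale.

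The reply is also right about size. A reader might take the complete-data gains as the expected benefit, or conclude that at least 5 percentage points of power are at stake for correlations up to 0.7. With deaths allowed for, that fails. In the heaviest-attrition scenario the gain is 4 points at ρ = 0.5 and 2 points at ρ = 0.7. That scenario itself depends on reading 60% and 75% as proportions of all enrolled; if they are proportions among deaths, survival is unknown.

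**Conclusion.** The point holds as a matter of precision, not validity. As stated, the main model for the repeated scales does not name the same-scale baseline score, and baseline data are assigned an exploratory role. If the analysis is run that way, the treatment estimate remains unbiased under randomisation but is less precise than it need be.

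Over the assumed range, the avoidable loss at month 12 is from 2 to about 13 points of power, relative to 80%. The upper end needs low correlation and complete data, so the lower and middle parts of the range are more plausible in a trial with many deaths. Every figure rests on an assumed correlation, equal across visits, and an assumed pattern of loss.

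The primary logistic analysis and the sample size are untouched. Only secondary outcomes are concerned, so this is a low-severity improvement, and it falls away if the separate analysis plan already makes the adjustment part of the main model.

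**What to change.** For QUALID, SAS, EQ5D and MCSI, state one main model:
- either a constrained longitudinal model, with baseline as the time-zero response and one baseline mean common to both arms;
- or a mixed model of the follow-up scores, with the baseline score of the same scale as a fixed covariate.

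Keep the group-by-visit terms and the random effect in either case. Leave other baseline characteristics exploratory, and say so separately, so that the baseline score of the outcome is not grouped with them.

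The cost is one sentence in the analysis plan, or a check that it is already there. No new data are needed, since all four scales are already collected before randomisation, and there is no material downside.

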### Participants and setting

We will enrol dyads of a person with dementia and their carer, with the carer as determined by relevant state legislation. People with dementia aged at least 65 years old attending one of six enrolling EDs will be screened after attendance for trial inclusion and exclusion criteria. The EDs are all metropolitan tertiary referral EDs located in Melbourne, Perth and Sydney, Australia.

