### Randomisation and control arm

After baseline assessment by the recruiter, an intervention (CELPI) clinician will be notified by email and will randomly assign participants into one of the two study arms using a web-based randomisation service. This will ensure the recruiter, who will also conduct the three monthly follow up assessments, is blinded to the allocation arm. Randomisation will be in a 1:1 ratio stratified by city of enrolment.

Once randomised, the CELPI clinician, who will have a tertiary degree in a health discipline (e.g. psychology, occupational therapy) but not be a physician, will contact all participants regardless of allocation arm and provide education regarding publicly available resources for the carers of people with dementia. The clinician will have all details of the baseline assessment available to them, such that they will have sufficient information on the person with dementia and their carer, and not need to access hospital records. If in the control arm, the clinician will then have no further contact with the participant. Participants in the control group will receive usual care from all health professionals who are involved in their management during the 12-month follow up. No treatments will be withheld from the control group.

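### The primary logistic regression, as described, names no term for the stratification factor (city) and gives baseline data only an exploratory role; prespecified adjustment would be a free, modest gain in power

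*Protocol article*

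**What the plan says.** All references are to the protocol article.

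- **Randomisation and control arm:** "Randomisation will be in a 1:1 ratio stratified by city of enrolment". Participants and setting places the six emergency departments in three cities: "located in Melbourne, Perth and Sydney, Australia".
- **Statistical Analysis, primary outcome:** "The overall difference in proportion of participants dying in a preferred location between the intervention and control groups will be assessed using logistic regression". No covariate is named, and the model is called neither adjusted nor unadjusted.
- **Statistical Analysis, end of the paragraph on models:** "Inclusion of baseline data in regression models will be used to explore additional variation within dyad characteristics". This is the only sentence that gives baseline data a role. It follows the descriptions of the primary, repeated-measures and count models and is not tied to any one of them.
- **Statistical Analysis, opening:** "Publication of a full statistical analysis plan separate to this manuscript is planned".
- **Sample size:** the plan is to "assume 60% of people with dementia in the control arm of the trial will die in a carer preferred location" and "to have 90% power to detect a 15% increase in the proportion of people dying in preferred locations to 75" per cent, with 408 evaluable and 440 enrolled. On alpha: "The Type I error probability associated with these tests of this null hypothesis is 0.05".
- **Baseline assessment:** performance status (AKPS) and the nominated place of death are recorded before randomisation. The eligibility text admits people living in residential aged care or in the community.

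**The concern.** Stratifying by city forces the arms to balance within each city. If city predicts the outcome, an analysis that ignores it uses a standard error that is a little too large for the design, so the test is conservative.

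The second issue is usually the larger one. Whether a person dies in the nominated place plausibly depends on which place was nominated, where the person lives and how frail they are. All of this is recorded or knowable at enrolment. If such variables serve only for exploration, the confirmatory test gives up the power they offer. The choice of covariates is also left less firmly fixed than it could be.

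The effect scale belongs to the same decision. The stated target is a difference in proportions, whereas the natural output of a logistic model is an odds ratio. Adding covariates changes what that odds ratio means.

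**Working it through.** **1. Reproduce the plan's sample size.** Inputs from Sample size: p1 = 0.60, p2 = 0.75, power 0.90, alpha 0.05. Sidedness is not stated; two-sided is assumed because it reproduces the figure, whereas one-sided gives 332.

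n per arm = [z(0.975)·√(2·p̄·(1−p̄)) + z(0.90)·√(p1(1−p1) + p2(1−p2))]² / (p2−p1)², with p̄ = 0.675

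= [1.960·√0.43875 + 1.282·√0.4275]² / 0.0225 ≈ 202.8, so 203 per arm and 406 in total.

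This agrees with 408. Power at 204 per arm is 90.2%. The formula contains no covariate, so the planned power does not rely on adjustment.

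**2. Cost of omitting city and a covariate.** The article gives no outcome rates by city and no predictor strengths, so both are assumptions:

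- 408 participants, three equal cities, 1:1 allocation balanced within city.
- City shifts of −s, 0, +s on the logit scale. s = 0.3 corresponds to control rates of about 53/60/67%, and s = 0.6 to about 45/60/73%.
- One standard normal baseline covariate with log odds ratio b per SD.
- Intercepts set so that the marginal rates are 60% and 75%.
- Wald test at two-sided 5%, 4,000 simulated trials per row, all three models fitted to the same data. Simulation standard error is about 0.5 points for power (√(0.9·0.1/4000)).

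| s | b | Power, no covariates | + city | + city and covariate | Type I error, no covariates | Type I error, + city |
|---|---|---|---|---|---|---|
| 0 | 0 | 90.4 | 90.5 | 90.3 | 4.6 | 4.6 |
| 0 | 0.5 | 90.6 | 90.8 | 92.0 | 5.4 | 5.4 |
| 0 | 1.0 | 89.9 | 89.9 | 94.3 | 5.2 | 5.2 |
| 0.3 | 0 | 89.7 | 89.9 | 89.9 | 5.0 | 5.1 |
| 0.3 | 0.5 | 90.1 | 90.4 | 91.6 | 4.8 | 5.0 |
| 0.3 | 1.0 | 89.9 | 90.1 | 94.2 | 4.8 | 4.9 |
| 0.6 | 0 | 91.2 | 92.1 | 92.2 | 4.5 | 5.3 |
| 0.6 | 0.5 | 91.3 | 92.0 | 93.0 | 4.0 | 4.9 |
| 0.6 | 1.0 | 90.5 | 91.2 | 94.9 | 4.1 | 4.7 |

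City alone adds 0 to 0.9 points. A covariate with b = 0.5 (odds ratio e^0.5 ≈ 1.6 per SD) adds a further 1.0 to 1.2 points. With b = 1.0 (odds ratio e^1 ≈ 2.7 per SD) the further gain is 3.7 to 4.4 points.

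**3. A binary predictor instead.** Take residence (community or aged care) with logit shifts of −1/+1, which is an odds ratio of e^2 ≈ 7.4, and city shifts of −0.5/0/+0.5. Power is 89.2% with no covariates, 89.7% with city and 94.6% with city and residence, so residence adds 4.9 points. Type I error is 4.8 to 5.0%. At half that strength power is 90.5 / 91.2 / 92.7%, a further gain of 1.5 points.

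**4. Effect scale.** The design contrast is 75 − 60 = 15 percentage points. The same contrast as a marginal odds ratio is (0.75/0.25)/(0.60/0.40) = 3.0/1.5 = 2.0. With prognostic covariates in the model the treatment odds ratio becomes conditional and no longer corresponds directly to 60% against 75% (non-collapsibility). A risk difference standardised over the trial's baseline distribution keeps the scale of the design contrast.

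**The case against.** The strongest reply is that this reads silence as a decision. The article never calls the primary model unadjusted, a separate statistical analysis plan is announced, and covariate lists and effect measures are commonly left to it. The sentence on baseline data is loose: it says such data will be included, and it neither excludes city nor says covariates will be picked after seeing the results. Most of this stands, and it keeps the point small. What remains is that the article does give baseline data a role, and that role is exploratory. An analysis plan that makes adjustment confirmatory has to replace that wording, not just fill a gap.

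Three stronger readings are tempting, and the documents do not support them.

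- **That stratifying by city bought substantial precision which is now lost.** City alone is worth about 0 to 1 point of power.
- **That omitting city makes the test invalid or undermines the 408.** The test errs only towards caution, and 408 reproduces without any adjustment.
- **That adjustment would lift power to about 96%.** A run of 1,500 trials with the strong residence effect gave 96.3%, but the 4,000-trial run of that scenario gave 94.6%. Both rest on the assumed odds ratio of about 7.4, for which the article has no figure.

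It might also be argued that city matters because there is one CELPI clinician per state. After the shared education contact, however, the clinician has no further contact with the control arm. Clinician differences would therefore appear mainly as variation in the treatment effect between cities, which a city main effect does not capture.

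Which effect measure is reported first is largely a choice for the analysis plan.

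**Conclusion.** The point holds as a low-cost improvement to the analysis, not as an error in the design. As described, the primary model names no city term although city is the stratification factor, and baseline data are assigned to exploration. The consequence is mild conservatism if city differences are large (type I error 4.0 to 4.5% at s = 0.6, against 4.6 to 5.4% with small or no differences). The power forgone is about 0 to 1 point for city and about 1 to 5 points for a prognostic baseline covariate. The top of that range needs a strong predictor, and with no predictive value the gain is nil. All the power figures take the plan's 60% against 75% as given. City and covariate strengths are assumptions.

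**What to change.** Before unblinding, state in the analysis plan:

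1. **Primary model.** Logistic regression with treatment, city and a short prespecified set of baseline variables as confirmatory terms: residence (aged care or community), category of nominated location, and AKPS.
2. **Effect measure.** A standardised risk difference with 95% CI from that model, reported alongside the odds ratio, to match the stated difference in proportions.
3. **Repeated-measures models.** City and the baseline value of the outcome as prespecified terms, not as exploration.
4. **Exploratory sentence.** Restrict it to analyses beyond these.

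The cost is wording only. AKPS and the nominated location are already in the baseline assessment. Residence is known at enrolment, though the sponsor should confirm that it is recorded as a data item. The sample size need not change.

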### Economic Evaluation Plan

A trial-based economic evaluation will take the perspective of the health care funder. Health care and intervention costs will be collected over the trial period. We will collect data on the cost to deliver the intervention (including staff costs, training, capital costs and consumables) as well as human and other resource costs associated with inpatient hospital admissions, ED presentations and other health service contacts. Inpatient admissions will be costed based upon Australian Refined Diagnosis Related Groups costs from the National Hospital Cost Data Collection; ED presentations will be costed using data from Independent Hospital Pricing Authority. All costs and savings will be adjusted to the base year using published deflators, and, if needed, costs incurred beyond one year will be discounted using a standard 5% discount rate.

Using mean costs and mean health outcomes in each trial arm, the incremental costs per 1) hospital death avoided; and 2) hospitalisation avoided compared with control group will be calculated; results will be plotted on a cost-effectiveness plane. Bootstrapping will be used to estimate a distribution around costs and health outcomes, and to calculate the confidence intervals around the incremental cost-effectiveness ratios. One-way and multi-way sensitivity analyses will be conducted around key variables and a probabilistic sensitivity analysis will estimate joint uncertainty in all parameters. A cost-effectiveness acceptability curve will be plotted to provide information about the probability that the intervention is cost-effective, given willingness to pay for each unit of benefit gained.

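### The economic plan names no baseline adjustment of incremental costs, although prior-year hospitalisations are collected: a minor and avoidable loss of precision

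*Protocol article*

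**What the plan says.** The Economic Evaluation Plan describes the estimator as follows: "Using mean costs and mean health outcomes in each trial arm, the incremental costs per" hospital death avoided and per hospitalisation avoided are to be calculated against control. Uncertainty is handled by resampling: "Bootstrapping will be used to estimate a distribution around costs and health outcomes, and to calculate the confidence intervals around the incremental cost-effectiveness ratios". The further analyses listed are these: "One-way and multi-way sensitivity analyses will be conducted around key variables and a probabilistic sensitivity analysis will estimate joint uncertainty in all parameters". None of them is described as adjusted for a baseline characteristic.

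Three other places bear on the point:

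- Baseline assessment: the recruiter records hospitalisations over the preceding twelve months and confirms carer information against medical records where these are available.
- Randomisation and control arm: "Randomisation will be in a 1:1 ratio stratified by city of enrolment". Prior hospital use is not a stratification factor.
- Statistical Analysis: "Inclusion of baseline data in regression models will be used to explore additional variation within dyad characteristics". This sentence follows the outcome models, is framed as exploration and does not mention costs. The same section announces a fuller plan: "Publication of a full statistical analysis plan separate to this manuscript is planned".

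**The concern.** Two of the named cost items are inpatient admissions and ED presentations. Hospital use in the year before enrolment is a plausible predictor of hospital use afterwards, and the trial already collects it. The design does not balance it beyond what simple chance within each city provides.

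If the arms happen to differ in prior hospital use, part of that difference will appear in an unadjusted incremental cost. Bootstrapping reflects this variation in the width of the interval but does not remove it from the estimate, because resamples centre on the observed difference. The cost-effectiveness plane and the acceptability curve are then centred on the same point. At stake is some precision, and some protection against an unlucky allocation, in the economic evaluation.

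**Working it through.** **The plan's own figure.** The economic plan states no numerical target. The only trial figure used below is the enrolled number, 220 per arm, so the Sample size section was checked first. Inputs: 60% versus 75%, 90% power, type I error 0.05, taken as two-sided.

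- n per arm = [1.960 × √(2 × 0.675 × 0.325) + 1.282 × √(0.60 × 0.40 + 0.75 × 0.25)]² / 0.15² = 203, or 406 in total. This agrees with the stated 408 to within two participants.
- 1 − 408/440 = 7.3%, consistent with the stated allowance of under 10%.

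**Assumption.** Let r be the correlation between prior-year hospitalisations and follow-up cost. The documents give neither r nor a standard deviation (SD) of cost. The range 0.2 to 0.5 is assumed, and results are in SD of cost or in standard errors (SE) of the unadjusted difference.

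**Step 1: chance imbalance.** The SE of a standardised difference between arms is √(2/220) = 0.095. The 95% limit of imbalance is 1.96 × 0.095 = 0.187 SD. The median absolute imbalance is 0.674 × 0.095 = 0.064 SD.

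**Step 2: carry-over into the unadjusted incremental cost.** The expected shift is r × imbalance. The cost difference has the same standardised SE of 0.095, so the shift in SE units is r × 1.96 at the 95% limit and r × 0.674 at the median.

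| r | Shift at 95% limit | Shift at median imbalance |
|---|---|---|
| 0.2 | 0.037 SD = 0.39 SE | 0.013 SD = 0.13 SE |
| 0.5 | 0.093 SD = 0.98 SE | 0.032 SD = 0.34 SE |

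**Step 3: precision.** Linear adjustment multiplies the SE by √(1 − r²).

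- r = 0.2: √0.96 = 0.98, a 2% reduction. The gain equals 1/0.96 = 1.04 times the sample.
- r = 0.5: √0.75 = 0.866, a 13% reduction. The gain equals 1/0.75 = 1.33 times the sample.

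**Step 4: simulation.** There were 4,000 trials for each r, with 220 per arm, skewed costs, over-dispersed prior admissions and no true cost difference.

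| Result | r = 0.3 | r = 0.5 |
|---|---|---|
| Mean unadjusted difference (SD of cost) | −0.002 | 0.001 |
| Coverage of unadjusted 95% interval | 94.5% | 94.5% |
| SD of estimate, unadjusted | 0.097 | 0.097 |
| SD of estimate, adjusted | 0.092 | 0.084 |
| Mean unadjusted difference when imbalance exceeds +1.6 SE | +0.054 | +0.100 |
| Mean adjusted difference in the same trials | −0.004 | +0.002 |

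The unadjusted analysis is therefore centred correctly and covers as it should. Adjustment tightens it and removes the shift in trials with an unlucky allocation.

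**The case against.** The strongest reply is that nothing in the Economic Evaluation Plan is wrong. Four parts of it deserve an answer.

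- **The text does not say the means are raw.** A reader might infer that the plan commits to crude differences. The words raw, crude and unadjusted do not appear, and adjusted analyses also yield mean costs and outcomes by arm. This stands: the plan names no adjustment, but it does not exclude one.
- **Detail may sit elsewhere.** This is a condensed article, and a separate analysis plan is announced. This stands in part. That plan may cover costs, but it is announced under Statistical Analysis, and the economic section is itself specific about its estimator, bootstrap, discount rate and sensitivity analyses. A better use of data already collected can fairly be suggested against a method described at that level.
- **The method is valid.** A reader might infer that imbalance biases the incremental cost or invalidates its interval. Neither follows. Under 1:1 randomisation the arm-mean difference is unbiased, and the bootstrap interval already allows for chance imbalance. This stands fully. A reader might also suppose that an imbalance enters the cost difference one for one, but only r times the imbalance does.
- **The size is assumed.** No value of r is documented. Cost over follow-up also depends on survival time, which makes r harder to presume. The shift at the 95% limit is exceeded in only about one trial in twenty, and at r = 0.2 the gain in precision is negligible. This stands, which is why the median case is shown beside the limit.

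**Conclusion.** The point holds as a minor, free improvement to the economic evaluation. The plan describes a valid comparison of arm means and names no adjustment for a recorded, unstratified and plausible predictor of hospital cost. The exploratory sentence on baseline data in the Statistical Analysis section is not extended to costs.

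The benefit of adjusting is a 2% to 13% smaller standard error and removal of a chance shift that is modest in a typical trial and up to about one standard error at the 95% limit. Both figures rest on the assumed correlation of 0.2 to 0.5 and on 220 analysed per arm. With 204 per arm the standardised SE becomes √(2/204) = 0.099, and the figures in SE units do not change.

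The documents do not support calling this a bias or an error in the plan. The primary outcome, the sample size and the trial's conduct are untouched.

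**What to change.** In the Economic Evaluation Plan, state that incremental costs and outcomes will be estimated by regression on arm, prior-twelve-month hospitalisations and city of enrolment, with the increments taken as differences in predicted arm means. Seemingly unrelated regression, or a generalised linear model for cost, would serve. State also that the model will be refitted in every bootstrap resample used for the intervals, the cost-effectiveness plane and the acceptability curve, and that unadjusted arm means will be reported alongside.

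If adjustment is already intended, the same sentence settles the ambiguity. Writing it down before unblinding also prevents the choice being made after the costs have been seen. The cost is one sentence and a little more analysis, with no new data collection.
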